### Per protocol set

We define the per-protocol by the following criteria: only one study jaw per patient; minimum number of implants as indicated in Table 1; no poor general health, no bisphosphonate therapy, no mental disorder, and no drug abuse during follow-ups; X-ray examination after 36 months is available.

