**Fig. 2 Fig2:**
[figure not shown]
Mini dental implants presented in Fig. 1 after two weeks

Test group A (immediate loading/restoration):

If the insertion torque of all MDIs in the study jaw was ≥ 35 Ncm implants were immediately loaded. The female housings were seated on the ball attachments and picked-up using self-cured acrylic resin (Secure hard pick-up kit, 3 M ESPE, Seefeld, Germany). If the insertion torque of one MDI in the study jaw is < 35 Ncm all MDIs of this jaw were immediately restored by relining the dentures with a soft material (Secure soft reline kit, 3 M ESPE, Seefeld, Germany) embracing the ball heads. After 4 months, the soft base were substituted with the housings and acrylic resin (Fig. 3).

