**Fig. 3 Fig3:**
[figure not shown]
Housings for the implants presented in Fig. 2 were picked up after 4 months

Control group B (delayed loading):

The recesses for the female housings in the PRDP remained empty for 4 months. Thereafter, the housings were seated on the ball attachments and picked-up using self-cured acrylic resin (Secure hard pick-up kit, 3 M ESPE, Seefeld, Germany). In the case of mucosal hyperplasia around the implant before to the fourth months, the recesses should be relined earlier using the soft material.

During the study period and thereafter the participants will be treated by the dentists of the study sites according to their dental healthcare needs. Treatments could arise from study-related events, e.g. implant or tooth loss, prosthesis fractures or study-independent events, e. g. in the opposite jaw. Treatments before study closure will be considered as outcomes.

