### Stopping criteria

A participant will be excluded from the trial if (a) the insertion torque of one implant is <15 Ncm; (b) the patient shows intolerance/allergy to titanium; (c) the occurrence of any serious adverse events related to the implantation; (d) degradation in the health status that compromises the participation in the trial; (e) failure to comply with trial requirements; (f) the patient withdraws her/his consent. The examiner and the dentists of the treatment centers are committed to report the principal investigator on the occurrence of events promptly.

The study will be terminated if (a) more than 20 % of the implants fail in any group after implant placement; (b) recruitment will not reach 80 % of the estimated number of patients during the first year; (c) the response after the first year is < 80 % of included participants.

The criteria will be checked every six months after the inclusion of the first patient. Premature termination of the trial should be decided by principal investigator in agreement with the sponsor.

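### The per-protocol set never checks that the assigned loading was received and requires a 36-month X-ray, so it cannot show the effect of adhering to the loading protocol

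*Protocol article*

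**What the plan says.** The section Per protocol set of the protocol article lists every criterion:

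- "only one study jaw per patient; minimum number of implants as indicated in Table 1";
- adequate general health throughout follow-up, without bisphosphonates, mental illness or misuse of drugs;
- "X-ray examination after 36 months is available".

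The randomised factor is described under Interventions. In test group A, housings are picked up at once if every implant in the jaw reaches 35 Ncm. Otherwise "all MDIs of this jaw were immediately restored by relining the dentures with a soft material". For control group B the rule is "The recesses for the female housings in the PRDP remained empty for 4 months". The same paragraph makes an exception for mucosal hyperplasia before month 4, when "the recesses should be relined earlier using the soft material".

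Three other sections bear on the point. Under Primary outcome: bone level, the basic confirmatory model takes the 12-month (t4) and 36-month (t6) values as dependent variable. Additional notes declines imputation, partly because mixed models cope with data missing at random. Stopping criteria allows a participant to be removed from the trial for "failure to comply with trial requirements".

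**The concern.** A per-protocol analysis is normally read as the comparison among patients who received what they were allocated. Here none of the criteria concerns loading. They cover eligibility-type conditions, the number of implants and the availability of one late X-ray.

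Two things follow. The set does not separate patients who received their assigned loading from those who did not. It also selects on an event after randomisation, being X-rayed at 36 months, and so removes the earlier measurements of patients who lack that film. If the result were set beside the main analysis and the two agreed, a reader could take this as confirmation under adherence, which the set is not built to give.

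**Working it through.** **1. The criteria set against the treatment rules.** Take four hypothetical patients who meet the jaw, implant-number and health criteria:

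- *Allocated to A, neither picked up nor relined until month 4, 36-month X-ray taken:* in the set, although the assigned treatment was not given.
- *Allocated to B, housings picked up at placement, 36-month X-ray taken:* in the set, although the assigned delay did not occur.
- *Allocated to B, soft-relined before month 4 for hyperplasia, 36-month X-ray taken:* in the set. This patient was treated as the control-group text provides. However, the soft material is also how part of group A is "immediately restored by relining the dentures with a soft material", and the set does not mark the patient.
- *Either group, treated exactly as assigned, X-rayed at 12 months but not at 36:* out of the set.

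The first two cases show that adherence is not required for entry. The fourth shows that it is not sufficient.

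**2. The X-ray rule against the model.** The confirmatory model has two outcome times, t4 and t6. A patient with t4 only contributes one of two values to the mixed model and none to the per-protocol set. A patient with neither contributes to no analysis of this outcome. The cost of the rule is therefore the 12-month values of patients without a 36-month film. Their number is not given.

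**3. The plan's own sample size (Sample size section).** Inputs: difference 0.4 mm, SD 0.5 mm, two-sided alpha 0.05, power 80 %. The standardised effect is 0.4/0.5 = 0.8. A two-sample t-test gives n = 25.5, so 26 per group, with power 80.7 %. The stated figure reproduces. With 75 % response, 26/0.75 = 34.7, so 35 per group or 70 in total would suffice. The planned 80 leaves 80 × 0.75 = 60, or 30 per group, with power 86.1 %.

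**4. Illustrations only.** The article gives no rates, so the fractions below are assumptions.

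- *Early relining.* If a share f of B lost bone exactly like A, the difference would be 0.4 × (1 − f). For f = 10, 20 and 30 % this is 0.36, 0.32 and 0.28 mm, with power at 30 per group of 78, 68 and 57 %. The same dilution would be present in the as-randomised comparison, so these figures do not measure a fault of the per-protocol set. Behaving exactly like A is also an extreme assumption, because relining in B follows some time after placement.
- *Selection on the 36-month film.* Suppose the worst share s of A had no film, other losses were random, and bone loss were normal. The observed A mean would be 0.9 − 0.5 × φ(z)/(1 − s), where z is the upper-s normal quantile. For s = 5, 10 and 15 % the difference from 0.5 becomes about 0.35, 0.30 and 0.26 mm. This shows a possible direction only. The 36-month values would be missing from the main model too; the rule additionally discards the 12-month values.

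**The case against.** The best defence is that this is a completer-type set beside a mixed model that already uses all available data, and that such sets are common. The article does not say which analysis uses the set, and the sensitivity analyses listed for the primary outcome do not mention it. Loading in group A follows directly after the envelope is opened, which leaves little room for non-receipt, and the stopping rule on non-compliance might remove some patients who were not treated as assigned. Much of this stands, and it limits the consequence. It does not repair the definition: the stopping rule is general, does not mention loading and is not part of the per-protocol list.

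Four stronger readings are tempting, and the document does not support them:

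- *That controls relined early are crossovers who should be removed.* The control-group text itself provides for the relining, so these patients are not deviators. Excluding them would select on mucosal response in one arm.
- *That the power losses above measure this defect.* They rest on assumed shares and apply equally to the as-randomised analysis.
- *That the X-ray rule removes about 20 of 80 patients.* The Discussion says the 25 % allowance is also meant to cover stopping criteria such as low insertion torque, and under Interventions those exclusions come before allocation.
- *That the rule removes patients because an implant was lost.* It is a patient-level condition on a panoramic film. A patient who loses one implant can still be X-rayed, and a lost implant has no 36-month bone level in any analysis. Selection of that kind could arise only through patients who drop out or are not X-rayed, for example after losing all implants, and nothing in the text quantifies it.

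**Conclusion.** The point holds in a limited form. As written, the per-protocol set contains no criterion on receipt of the randomised loading and conditions on a post-randomisation event. It therefore cannot be interpreted as the effect of adhering to the loading protocol, and it drops valid 12-month bone levels that the plan's own model can use.

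This rests on reading the definition as the closed list it presents itself to be. The size of any bias or loss cannot be computed from the document. The primary result is not shown to be affected, since the confirmatory model is not stated to rest on this set. The change is still worth making, because the rule is stated explicitly and correcting it costs almost nothing.

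**What to change.** 1. Add a criterion to the per-protocol definition: loading or restoration was delivered as the protocol prescribes for the assigned group.
2. Replace the 36-month X-ray condition with at least one post-baseline radiograph at t4 or t6, and let the mixed model use whatever is available.
3. Keep group B patients who were soft-relined early under the control-group provision, but flag them, report their number and timing, and give a supportive sensitivity analysis without them.
4. Reconcile the group A text, the group B text and the per-protocol definition on how early soft relining is counted in the analysis. This concerns classification only; no change to the clinical rule is implied.
5. State which analysis uses the set, and keep the as-randomised analysis primary.

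The cost is analysis-plan wording, best settled before the group comparison is run. Someone must also confirm that loading received and relining dates were recorded; the article does not say so. The sensitivity analysis in item 3 selects on mucosal response in one arm only, so it can be no more than supportive.

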### Evaluation of safety and tolerability

Because the sample size on patient level is low, we do not analyse differences between groups but describe vital signs and clinical adverse events with type, time, and severity.

### Additional notes

We do not impute missing data for two reasons. First, we choose mixed models, which are robust to missing data at random [45]; second, an imputation on four levels for this small sample of about 80 patients can hardly be justified [46]. For model checking and sensitivity analysis we use a variety of methods [45, 47]. For subgroup analysis of jaw classification, the two-sided alpha level will be reduced from 0.05 to 0.025.

An interim analysis will not be done. A statistician (CS) blinded to the study groups will perform the calculations by using up-to-date versions of STATA (StataCorp LP, College Station, Texas, USA) and R for windows, Version 2.12.2 (R Foundation for Statistical Computing, Vienna, Austria).

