### Primary outcome: bone level

Because jaw was used for randomization, we extend Gilthorpe’s mixed model by inserting jaw to levels for patient, tooth, and site [38] and adjust for model complexity by using the Kenward-Roger correction [39]. To ensure hierarchical levels, tooth positions within each jaw are coded from 1 to 16 instead of from 1 to 32 on patient level. The first adjustment set consists of risk factors of periodontal disease including age, gender, and smoking [40]; and design variables including centre, jaw [41], jaw classification, and time. Because X-ray at t_0_ is assessed before differentiating treatment in groups, it is a baseline measurement which can additionally be used to increase efficiency [42]. Note also the discussion on pages 158–160 in Harrell’s textbook [43]. The syntax of the basic confirmatory model with the highest statistical power for the factor group is (Stata’s version 14):

Here, only the time points t_4_ and t_6_ are used as dependent variable (Table 2). To interpret changes after 12 and 36 months in exploratory analyses, we include t_0_ as dependent variable:

In sensitivity analyses, we allow for continuous time instead of points in time, for correlated random effects, or for random effects of other than tooth level and suspend the Kenward-Roger correction. In the second adjustment set, jaw classification is replaced by patient’s mean probing depth before randomization; in the third and fourth set, school education will be added to the first and second set, respectively.

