### Tertiary outcomes

See Table 2 for priority ordering. We allow for nonlinear change as described above. If possible we adjust for values before treatment [40, 43]. The confirmatory and the exploratory model of periotest for teeth:

For tertiary outcomes other than periodontal or peri-implant conditions, we expect differences between groups before housing in group B (time points t_1_ and t_2_) but no differences after that (time points t_4_-t_6_). Thus, we present only confirmatory analyses. The model for food frequency questionnaire at time points t_1_ and t_2_:

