### Recruitment

Suitable patients were recruited via personal information during standard recall in two steps. Patients with a suitable dental status were asked whether they were satisfied with their PRDP. After signed informed consent, patients that are unsatisfied with their RPDP were screened according to the inclusion and exclusion criteria. Patient with treatment need, i.e. technically inacceptable RPDP, periodontitis, caries, but who otherwise met the inclusion criteria received firstly an adequate dental and/or prosthodontic treatment, Thereafter, they were re-examined.

All patients were evaluated by the calibrated examiner. Patients meeting the dental, medical, and prosthodontic inclusion criteria, were radiographically examined using panoramic X-ray with a reference marker (titanium tube, steel pin, steel ball) to determine whether the residual bone of the jaw meets the inclusion criterion: to place the MDIs without augmentation procedures. In order to achieve comparable treatment plans, the TC assessed the X-rays and pseudonymized documents of each patient to check and, if necessary, to correct the original treatment plan of all centres. If all inclusion criteria were met, patients were included in the study. In addition to the pre-treatment examination, the baseline characteristics (age, gender, medical history, smoking habits, oral health behaviour, school education, household income) of the study participants were assessed by a questionnaire. The schedule of recruitment was 17 months (First Patient in 01.11.2013, last Patient in: 31.03.2015).

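### The no-imputation rule is justified for missing outcomes only, so patients with a missing patient-level baseline covariate would leave the models although their outcome was observed

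*Protocol article*

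**What the plan says.** Additional notes sets one rule for all missing data and supports it with two reasons: "We do not impute missing data for two reasons. First, we choose mixed models, which are robust to missing data at random" and "second, an imputation on four levels for this small sample of about 80 patients can hardly be justified". It does not separate outcomes from covariates.

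The models carry several covariates. For the primary outcome, "The first adjustment set consists of risk factors of periodontal disease including age, gender, and smoking", together with centre, jaw, jaw classification and time. The radiograph taken at implant placement also enters the confirmatory model, because "it is a baseline measurement which can additionally be used to increase efficiency". The second set exchanges jaw classification for the patient's mean probing depth, and "in the third and fourth set, school education will be added to the first and second set, respectively". For the tertiary outcomes the article says "If possible we adjust for values before treatment". Table 2 lists the pre-treatment OHIP-G14, satisfaction, food frequency, food avoidance and chewing values at patient level.

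The Recruitment section shows where the self-reported covariates come from: "school education, household income) of the study participants were assessed by a questionnaire". Smoking is in the same list.

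**The concern.** The rule is wider than its justification. A likelihood-based mixed model copes with a missing response under missing at random, because the patient's other responses stay in the likelihood. It makes no such provision for a missing covariate: the record cannot be evaluated and the software omits it. Smoking or education is constant within a patient, so one missing value removes all of that patient's implants, sites and visits.

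Two things are at stake. Randomised patients with observed bone levels or questionnaire scores would be excluded without need. And the four adjustment sets, which should show whether the result depends on the choice of covariates, could differ because they use different patients.

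**Working it through.** **1. Does either reason cover the missing value?**

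| Missing value | Robust under missing at random? | Needs four-level imputation? |
|---|---|---|
| Outcome at one visit | Yes | Yes, for implant- or site-level outcomes |
| Smoking, education | No, the record is omitted | No, one value per patient |
| Pre-treatment OHIP-G14, satisfaction, food or chewing value as covariate | No, the record is omitted | No, one value per patient |

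Both reasons apply to the first row and neither applies to the other two.

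**2. What happens to the records?** Take 60 patients with two visits, which is 120 records.
- Six patients each miss one outcome: 120 - 6 = 114 records, and all 60 patients stay in the fit.
- The same six have both outcomes but no smoking value: 120 - 12 = 108 records, and 54 patients remain.
- Smoking filled at patient level: 120 records and 60 patients again.

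**3. The plan's own sample size (section Sample size).** Inputs are a difference of 0.4 mm, SD 0.5, two-sided 0.05 and 80 % power, so d = 0.4/0.5 = 0.8. The two-sample t-test needs 25.52, rounded up to 26 per group, with power 0.807 at 26. The stated figure is reproduced. With 40 allocated per group and 75 % response, 40 × 0.75 = 30 per group are evaluable, with power 0.861.

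**4. Size of the loss.** The article gives no missing rates, so 2-5 % per covariate is an assumption, with missingness independent between covariates.
- Confirmatory primary model, smoking only: loss of 2-5 %. At 2 %, 30 × 0.98 = 29.4 per group, power 0.854. At 5 %, 30 × 0.95 = 28.5 per group, power 0.843.
- Sets 3-4, smoking and education: 1 - 0.98² = 0.040 and 1 - 0.95² = 0.098, so about 4-10 %. At 10 %, 30 × 0.90 = 27 per group, power 0.822.
- Slack: at 13 % loss, 30 × 0.87 = 26.1 per group, so the required 26 is still met.

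These powers use the plan's patient-level t-test and show only the scale of the loss. Missing mean probing depth in sets 2 and 4 would add to it.

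**The case against.** The strongest reply is that little is at risk in the confirmatory analysis. Centre and jaw are stratification factors, jaw classification is needed for eligibility, and age and gender are seldom missing. Among the patient-level covariates that leaves smoking, one question put to about 80 patients. Range checks are planned to find missing values, and recruitment had finished at submission, so the covariates may already be complete. All this stands and keeps the point modest. It does not make the stated reasons fit the rule.

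Other limits also stand. The article nowhere says that such patients are dropped; this follows from the rule together with the usual behaviour of the named commands. The model syntax was not readable in the text used here, so the covariate lists come from the prose and Table 2. Adjustment for pre-treatment values is planned only where possible.

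A reader might infer three stronger points that the document does not support.
- *One skipped questionnaire item voids a score or drops the patient.* The article states no item rule, and scoring may be left to the analysis plan or the instrument manual. An unusable follow-up score would cost only that visit.
- *An unreadable film at placement loses an observed outcome.* The outcome is change from that film, so the change was not observed. In the exploratory model "we include t_0_ as dependent variable", which keeps such implants, and a patient-level fill would not repair them in the confirmatory model.
- *Power of the primary test falls from 0.86 to 0.82.* That loss needs about 10 % missing, which under the assumed rates arises only in sets 3-4. It also stays above 80 %.

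**Conclusion.** The point holds for patient-level baseline covariates. The rule is unrestricted, neither reason extends to these variables, and a standard fit would exclude randomised patients whose outcomes were observed.

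Under the assumed 2-5 % missing per covariate, the effect on the confirmatory primary model is small and does not bring power below the planned 80 %. The clearer harm is to the comparison of adjustment sets: with 2-5 % missing in sets 1-2 and 4-10 % in sets 3-4, a change in the estimate cannot be put down to the added covariate alone. In the tertiary models a missing pre-treatment score would remove the patient entirely; the food frequency model, for instance, uses only the 0.5- and 4-month visits. If all covariates prove complete, the effect is nil and only the wording needs correction.

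**What to change.** - Limit the rule to outcomes, for example: 'Missing outcome values are not imputed.'
- Fill a missing patient-level baseline covariate with its overall mean across both groups, before any spline terms are formed. For smoking and education a 'missing' category is an alternative. Either is acceptable because these values belong to the pre-treatment assessment and the envelope is opened only after implant placement, so the filled value cannot depend on allocation.
- Where only one or two patients lack the value (2-5 % of 60 is about 1 to 3), fill the category indicators with their overall means, since a separate category that small would largely use up those patients' information.
- Run adjustment sets 1-4 on the same patients and report the number filled per covariate and group.
- For implants without a readable film at placement, use the already planned model with that film as a response as a check.

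The cost is a few lines in the plan and code, with no new data. The downside is slightly weaker adjustment for the filled patients.
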